**Methods:**

Using a pragmatic, sequential, cluster randomized trial design; we will compare the effectiveness of two cervical cancer screening models for self-collected HPV testing: 1) community health worker recruitment (door-to-door); and 2) community health meetings. In Mayuge district, Uganda, 31 villages are randomized to one of two treatment arms. Due to the nature of this trial, blinding is not possible. Women are eligible to participate if they have no previous history of hysterectomy or treatment for cervical cancer or pre-cancer and are aged 25–49 years old. All participants receive an integrated package of cervical cancer screening and education. Samples are tested for HPV using GeneXpert point of care testing. All women who test positive for HR-HPV types are referred to a designated health centre for follow-up inspection by Visual Inspection with Acetic acid (VIA) and treatment with thermal ablation. The primary outcome for the trial is the number of women who attend follow-up for VIA screening at a designated Health Centre after a positive HR-HPV test out of all women screened per arm. Secondary outcomes include: cervical cancer screening knowledge; patient-reported experience measures for self-collected cervical cancer screening; and HPV incidence.

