## Methods

### Objectives

The primary objective of this study is to compare cervical cancer screening follow-up completion using two implementation approaches for self-collected HR-HPV testing in a rural, low-resource setting: 1) community health workers recruiting women door-to-door and 2) community health meetings. Secondary objectives of the trial are to compare cost-effectiveness of each cervical cancer screening model measured by the incremental cost-effectiveness ratio (ICER) and reduction in lifetime cervical cancer risk for each study arm and to conduct a process evaluation guided by the Reach, Effectiveness, Adoption, Implementation, Maintenance (RE-AIM) framework [18] focused on barriers and facilitators of implementation, implementation reach and fidelity for each model of cervical cancer screening used.

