					4.1 Instruction on how to perform a behaviour
					6.1 Demonstration of the behaviour
					12.5 Adding objects to the environment
Program adherence (Follow-up and treatment)	How effective was the program at increasing CCS follow-up and treatment among participants?	CHW informs participants of their screening results. HR-HPV+ participants are referred for follow-up at HCII or HCIII and asked to set a date for follow-up/treatment.	Increased follow-up and treatment among HR-HPV+ participants	Follow-up/treatment attendance at each level of the pathway to care compared between arms	1.1 Goal setting (behaviour)

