### Study outcomes

Study outcomes were determined by applying RE-AIM framework [18] to intervention objectives. The primary outcome for this trial is measured at the individual level as positive or negative attendance for follow-up VIA screening (endline) at a designated Health Center after a positive HR-HPV test, among all participants screened per arm.

Secondary outcomes compared between arms include:
Cervical cancer screening knowledge measured as the count of correct responses to knowledge questions per individual within 6 months of recruitment.Patient-reported experience measures for self-collected cervical cancer screening at intervention completion at the individual level within 6 months of recruitment.HPV incidence at baseline as a sensitivity analysis to test our assumption of equal distribution of HR-HPV among the study population.

A summary of objectives, outcomes and analysis plans can be found in Table 2.

**Table 2 Tab2:** ASPIRE Mayuge Evaluation Strategy

Research Objective	Research Question	RE-AIM Outcome	Outcomes	Data Analysis Approach
Primary Objective				
Self-collected cervical cancer screening effectiveness				
To compare the effectiveness of two self-collected CCS models at improving VIA follow-up: community health worker recruitment (door-to-door) versus community health day.	Which of the two self-collected CCS models is more effective at improving VIA follow-up among screened women: door-to-door screening or community health days?	Effectiveness (Individual level)	Primary Outcome: Follow-up attendance for VIA screening at a designated Health Center after a positive HR-HPV test out of all participants screened per arm	Quantitative analysis of clinical data: Mixed effect model with cluster as a random intercept and adjusted for all known confounders. Intention to treat and sensitivity analysis; Multivariate logistic regression
	What is the: prevalence of HR-HPV types; incidence of cervical cancer; association between HPV and STIs (gonorrhea and chlamydia); and risk difference in VIA follow-up between WLWHA vs non HIV?	n/a	HR-HPV prevalence; cervical cancer incidence; STI-HPV association; HIV-HPV association; Risk difference in VIA follow-up attendance between WLWHA vs. non HIV	Quantitative analysis of clinical and survey data: Descriptive statistics: prevalence, incidence; Bi-variate analysis: adjusted odds ratio, Risk difference (adjusted for cluster and other confounders)

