### Statistical analysis

#### Primary objective

Statistical analysis will be performed in R Statistical software using the clusterPower package [28] with an intention to treat approach. The primary outcome rate will be computed for each cluster and each study arm and ICCs calculated to assess cluster level variability prior to the primary analysis. The primary effectiveness measure will be compared between arms by estimating a mixed effect logistic regression model with cluster as a random intercept. The model will be adjusted for all known confounders at the individual and cluster level. There is no planned midpoint evaluation as no serious safety concerns are expected.

Apparent prevalence of HPV and STIs will be estimated in the study regions using trial data. Population prevalence of CIN2+ will be estimated based on this apparent prevalence using the reported sensitivity and specificity of the GeneXpert HPV test for this disease status (Table 5).

**Table 5 Tab5:** Diagnostic test characteristics for moderate and severe cervical lesions

	CIN2+	CIN3
Sensitivity	90.8%(84.7–95.0%)	92.3%(84.8–96.9%)
Specificity	42.6%(38.5–46.9%)	40.0%(36.1–44.0%)

Secondary outcomes compared between arms will be estimated in a similar manner. The effect of each study arm on HPV incidence is estimated using a multi-level logistic regression model as per the primary analysis. The effect of each study arm on CCS knowledge and patient experience will be estimated using a multi-level Poisson model, adjusted for the same individual and cluster level confounders with the addition of HPV status as an individual compounder and with person-time in follow-up as an offset.

Planned secondary analyses include estimating the group by arm interaction of HIV and other STI status on effectiveness of each CCS model. This will be done by adding an interaction term for each comorbidity and arm in the primary model. Temporal trends in HPV incidence and follow-up will be presented graphically.

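### The primary outcome multiplies HR-HPV positivity by VIA attendance, so it cannot by itself isolate follow-up completion, and no comparison among HR-HPV-positive women is named as primary or key

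*Protocol article*

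**What the plan says.** The denominator is the same wherever the primary outcome is defined. Study outcomes counts attendance "after a positive HR-HPV test, among all participants screened per arm", the abstract has "after a positive HR-HPV test out of all women screened per arm", and Table 2 has "after a positive HR-HPV test out of all participants screened per arm". The abstract also fixes who can have the event: "All women who test positive for HR-HPV types are referred to a designated health centre for follow-up inspection". The arm 1 and arm 2 descriptions likewise invite only women with a positive result to book a VIA visit.

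The primary objective is to "compare cervical cancer screening follow-up completion using two implementation approaches", and Table 2 words the research question in terms of screened women. The adherence row of Table 1 gives as its outcome "Increased follow-up and treatment among HR-HPV+ participants", with attendance at each step of the care pathway compared between arms.

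The dependence on HPV positivity is acknowledged. One secondary outcome is "HPV incidence at baseline as a sensitivity analysis to test our assumption of equal distribution of HR-HPV among the study population". The primary analysis is planned by "estimating a mixed effect logistic regression model with cluster as a random intercept", adjusted for known confounders that are not listed. HPV status is named as an added covariate only for the knowledge and experience models.

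**The concern.** An HR-HPV-negative woman is not referred for VIA, so she is a non-event however well the programme performs. The arm contrast therefore responds to two things: how many screened women test positive, and how many of those attend. Only the second is follow-up completion.

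Randomising villages makes the underlying HR-HPV prevalence equal in expectation. It does not guarantee that the women who are screened have equal positivity. Participants and recruitment describes home visits in arm 1 and attendance at a community health day in arm 2, and leaves women who decline self-collection out of the primary analysis. Trial design says that the arms are sequential. If route or calendar time shifts who is screened, positivity can differ systematically between arms, and the primary odds ratio would carry that difference under the name of follow-up. The Discussion says that the results will inform national scale-up, so the distinction matters to the reader of the result.

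**Working it through.** **Inputs from the protocol.** 15 villages per arm, 70 women per village, baseline follow-up 20%, increases of 10, 20 and 30 points, ICC 0.01 to 0.20 (Sample size, Table 4).

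**Assumed.** Two-sided alpha of 0.05 (not stated). HR-HPV positivity and attendance are not given, so every value below is illustrative.

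**Table 4 first.** Effective n per arm = 15 × 70 / (1 + 69 × ICC), with a two-proportion normal approximation and unpooled variance.
- ICC 0.05, 20% vs 30%: n = 1050/4.45 = 236; SE = √[(0.16 + 0.21)/236] = 0.0396; 0.10/0.0396 − 1.96 = 0.565; power 71% (stated 71%).
- ICC 0.10, 20% vs 40%: n = 1050/7.9 = 133; SE = √[(0.16 + 0.24)/133] = 0.0549; power 95% (stated 95%).
- All other cells agree within 2 points.

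**The outcome as written.** P(event) = P(HR-HPV+) × P(attend | HR-HPV+).

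| Positivity, arm A vs B | Attendance, A vs B | Outcome, A vs B | Odds ratio |
|---|---|---|---|
| 20% vs 25% | 80% vs 80% | 16% vs 20% | 1.31 |
| 25% vs 30% | 50% vs 50% | 12.5% vs 15% | 1.24 |
| 20% vs 30% | 50% vs 50% | 10% vs 15% | (0.15/0.85)/(0.10/0.90) = 1.59 |
| 30% vs 20% | 40% vs 60% | 12% vs 12% | 1.00 |

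The first three rows show an arm effect where attendance does not differ. The last hides a 20-point difference in attendance. With 15 × 70 women per arm, the third row would be declared significant about 76% of the time at ICC 0.01 and 37% at ICC 0.05.

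**The planned check on HPV.** For 20% vs 25% positivity, ICC 0.01: n = 1050/1.69 = 621; SE = √[(0.16 + 0.1875)/621] = 0.0237; power about 56%. At ICC 0.05 it is about 26%. For 20% vs 30% the sum is the first column of Table 4: 98% and 71%. A large imbalance would often be seen and a moderate one often missed. In neither case does the primary estimate change.

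**Table 4 and the denominator.** The all-screened proportion cannot exceed positivity, so a rate of 50% needs positivity of at least 50%. With an HR-HPV-positive denominator, the cluster size is the expected number of positives. At an assumed 25% positivity this is 70 × 0.25 = 17.5 per village:

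| ICC | 20% vs 30%: Table 4 → positives only | 20% vs 40%: Table 4 → positives only |
|---|---|---|
| 0.01 | 98% → 69% | >99% → >99% |
| 0.05 | 71% → 50% | >99% → 96% |
| 0.10 | 47% → 37% | 95% → 87% |
| 0.20 | 28% → 25% | 75% → 68% |

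For 20% vs 40% at ICC 0.05, power among positives runs from 90% (positivity 15%) to 99% (positivity 40%).

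**The case against.** The denominator is deliberate. It is used consistently and matches Table 2's question, and attendance per woman screened is a sound measure of what a programme delivers. This stands: the outcome answers a real question, and Table 1, which maps behaviour change techniques, does not define the primary outcome differently.

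Chance differences in HR-HPV prevalence between villages are variance, which the random intercept addresses; they are not bias. This also stands. Only a systematic difference through recruitment or timing would bias the reading, and the protocol supports calling that possible, not likely.

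Step-specific comparisons are foreseen: Table 1 mentions attendance at each pathway step by arm, and Table 2 lists participation and attrition by step. This is partial mitigation. Neither is named as a primary or key analysis, no model is attached, and the Table 2 items are mainly descriptive.

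Restricting to positives does not restore the protection of randomisation, because that set is formed through the same recruitment routes plus a test result. True: it removes the positivity factor and leaves the selection.

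Three stronger readings are tempting and unsupported.
- A reader might infer that the HIV risk difference is distorted in the same way. Table 2 does not state its denominator; only the HIV interaction, added to the primary model, clearly inherits the issue.
- A reader might infer that Table 4's rates are impossible. Positivity is not given, and the Table 5 specificity for CIN2+ (42.6%), taken literally, implies positivity of at least about 57%, so the ceiling need not bind.
- A reader might infer a large loss of power. At 25% positivity, 20% vs 40% attendance becomes 5% vs 10%, with 54% power at ICC 0.05 against 96% among positives. That holds the ICC equal on both scales. If positivity is constant across villages, an attendance ICC of 0.05 becomes roughly 0.25 × 0.05 × 0.80/0.95 = 0.011 on the all-screened scale, where power is about 91%. The two figures are therefore not like for like.

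**Conclusion.** The point holds in a limited form. By its definition the primary outcome is positivity times attendance, and it reads as a comparison of follow-up completion only if positivity is equal between arms. The protocol states that assumption and plans a test that can neither establish it nor correct the estimate. No model-based comparison among HR-HPV-positive women is named as primary or key.

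The direction of any distortion is unknown. The illustrations give odds ratios of 1.24 to 1.59 with no difference in attendance, and 1.00 with a 20-point difference. They rest wholly on assumed positivity and attendance and show what could happen, not what to expect. The documents do not support saying that the all-screened outcome is invalid, that it answers no useful question, or that bias is likely.

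**What to change.** - Prespecify the same mixed-effect logistic model for VIA attendance among HR-HPV-positive women, either as the primary analysis or as a named key analysis beside the all-screened yield. Use this set for the HIV interaction as well.
- State that the conclusion on follow-up rests on the HR-HPV-positive analysis, and that the all-screened proportion is read as programme yield.
- Report baseline HR-HPV prevalence by arm next to both results, and call it prevalence; a single baseline test does not measure incidence.
- Restate Table 4 for the denominator used: expected positives per village if HR-HPV-positive, or rates consistent with an explicit positivity if all screened.

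No new data are needed, because the laboratory result logs and VIA logs are already audited. The costs are fewer women analysed, a power statement that may be less favourable (for example 50% where Table 4 shows 71%, at 25% positivity), and, if the primary outcome itself is replaced, an amendment to a registered outcome; the key-analysis option leaves that outcome in place. Selection through the recruitment route remains under either denominator and should be acknowledged as a limitation.

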### Participant timeline

A time line of study activities can be found in Table 3.

**Table 3 Tab3:**
[figure not shown]
Schedule of study activities for the ASPIRE Mayuge trial

### Sample size

Sample size for the study was restricted to the 31 villages in the region available for randomization. Power was estimated using R statistical software across a range of plausible interclass correlation coefficients (ICCs) and absolute changes in follow-up rate from the baseline of 20% in one study arm. Power calculations assumed 15 clusters per study arm with an average size of 70 women per cluster. Power estimates were repeated using a cluster size of 50 women per village with negligible effect. Using these assumptions, we are adequately powered for a 20–30% absolute change in the outcome rate between the study arms, and up to 10% absolute change if low heterogeneity in clusters is found (see Table 4).

**Table 4 Tab4:** Power to detect difference in follow-up simulated across a range of ICCs and effect sizes

ICC	10% absolute increase in follow-up	20% absolute increase in follow-up	30% absolute increase in follow-up
0.01	98%	> 99%	> 99%
0.05	71%	> 99%	> 99%
0.10	47%	95%	> 99%
0.20	28%	75%	98%

A sup-group of women from each arm will complete a follow-up survey to assess cervical cancer screening knowledge retention and patient experience within six months of enrollment. Cluster stratified random sampling was used to select a subset of 25 participants from each cluster to total 375 participants from arm 1 and 400 from arm 2 for this survey. The survey sample size was calculated using a fixed number of clusters [23]; an ICC of 0.5; and assuming a mean knowledge score of 8 in arm 1 and 6 in arm 2 with a coefficient of variation of 1 for this score. Based on these assumptions 25 participants per cluster would result in 83% power to detect this target difference.

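### Table 4 counts all 70 women per village at a 20% follow-up rate, although only HR-HPV-positive women can have the primary outcome; the 10-point power claim is the main casualty

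*Protocol article*

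**What the plan says.** The Sample size section fixes the design at 31 villages and gives the power inputs: "Power calculations assumed 15 clusters per study arm with an average size of 70 women per cluster", and "absolute changes in follow-up rate from the baseline of 20% in one study arm". Table 4 then gives power for increases of 10, 20 and 30 points at ICCs of 0.01, 0.05, 0.10 and 0.20. The section concludes that "we are adequately powered for a 20–30% absolute change in the outcome rate between the study arms". It extends this claim to a 10-point difference, provided that villages turn out to differ little from one another. It also reports a sensitivity check: "Power estimates were repeated using a cluster size of 50 women per village with negligible effect".

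The Study outcomes section defines the primary outcome as VIA attendance "after a positive HR-HPV test, among all participants screened per arm". The abstract has the same denominator: "after a positive HR-HPV test out of all women screened per arm". The abstract sends only women with a positive HR-HPV test to VIA. The Sample size section does not say whether the 70 women or the 20% refer to screened or to HR-HPV-positive women, and it uses no HR-HPV positivity figure.

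**The concern.** The two main inputs do not clearly belong to the same outcome. A rate of 20% rising to 50% looks like attendance among women who tested positive. Seventy women per village looks like the number screened. Combining them lets women who cannot have the event count as if they could.

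Table 4 is the only power statement for the primary outcome. If it is too favourable, a null result will be read against more power than the trial had, above all for a difference of about 10 points.

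**Working it through.** **Inputs.** From the Sample size section: 15 clusters per arm, m = 70 (or 50), baseline 20%, increases of 10, 20 and 30 points, ICC 0.01 to 0.20. Assumed: two-sided alpha 0.05 (not stated) and HR-HPV positivity q of 15–35% (no planning value is given).

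**Formulas.** Design effect DE = 1 + (m − 1) × ICC. Effective n per arm = 15m / DE. Standard error = √{[p1(1 − p1) + p2(1 − p2)] / n}. Power = Φ(|p2 − p1| / SE − 1.96).

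**Step 1: reproduce Table 4 (m = 70).** At ICC 0.01 and 20% vs 30%: DE = 1 + 69 × 0.01 = 1.69; n = 1,050 / 1.69 = 621.3; SE = √(0.37 / 621.3) = 0.0244; power = Φ(4.10 − 1.96) = 98.4%.

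| ICC | +10: computed (stated) | +20: computed (stated) | +30: computed (stated) |
|---|---|---|---|
| 0.01 | 98.4% (98%) | >99% (>99%) | >99% (>99%) |
| 0.05 | 71.4% (71%) | 99.8% (>99%) | >99% (>99%) |
| 0.10 | 47.4% (47%) | 95.4% (95%) | >99% (>99%) |
| 0.20 | 28.3% (28%) | 75.9% (75%) | 97.7% (98%) |

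The table is arithmetically sound for 70 contributing women per village.

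**Step 2: read the rates as shares of all screened women.** Event rate = q × attendance among positives, so it cannot exceed q. The baseline of 20% needs q of at least 20%, and the comparison arm needs q of at least 30, 40 or 50%, even if every positive woman attends.

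**Step 3: read the rates as attendance among positives, with 70 women screened.** Then m = 70q, which is 10.5 at 15% and 24.5 at 35%. Worked case, q = 25%, ICC 0.01, 20% vs 30%: m = 17.5; DE = 1.165; n = 262.5 / 1.165 = 225.3; SE = √(0.37 / 225.3) = 0.0405; power = Φ(2.47 − 1.96) = 69%.

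| ICC | +10 (stated) | +20 (stated) | +30 (stated) |
|---|---|---|---|
| 0.01 | 51–81% (98%) | 97 to >99% (>99%) | >99% (>99%) |
| 0.05 | 40–57% (71%) | 91–98% (>99%) | >99% (>99%) |
| 0.10 | 31–41% (47%) | 81–91% (95%) | about 99% or more (>99%) |
| 0.20 | 23–26% (28%) | 64–72% (75%) | 93–96% (98%) |

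**Step 4: keep the stated all-screened denominator (m = 70) with the same attendance among positives.** For 20% vs 30% the rates become 3% vs 4.5% (q = 15%) up to 7% vs 10.5% (q = 35%). The ICC also changes scale. If positivity is equal across villages, between-village variance is q² × ICC × f(1 − f) and total variance is qf(1 − qf), so ICC(all) = q × ICC × (1 − f) / (1 − qf), where f is mean attendance among positives.
- +10 points, attendance ICC 0.01: 41–74% with the ICC rescaled, 29–59% with 0.01 carried over unchanged. The span is about 29–74%, against 98% stated.
- +20 points, attendance ICC 0.10 (f = 0.30): ICC(all) = 0.15 × 0.10 × 0.70 / 0.955 = 0.011, up to 0.35 × 0.10 × 0.70 / 0.895 = 0.027. Power is about 71–87%, against 95% stated.

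**Step 5: 50 women per village.** With all 50 contributing, 10-point power at ICC 0.01 is 95.8% against 98.4%, and at ICC 0.05 it is 67.9% against 71.4%. With positives only at q = 25% and ICC 0.01, m falls from 17.5 to 12.5: DE = 1.115, n = 187.5 / 1.115 = 168.2, and power falls from 69% to 57%.

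**The case against.** A reader might infer that the stated power is not delivered under any denominator. The document does not support that. If the 70 are HR-HPV-positive women, Table 4 holds exactly. The text does not exclude this, although it would need 70 / 0.35 = 200 to 70 / 0.15 = 467 screened women per village. With positives as the denominator, 20-point power is at least 81% up to ICC 0.10 and 30-point power at least 93% throughout, so it would also be wrong to say that the design could not see a difference.

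A reader might also carry the ICC unchanged to the all-screened scale and report 22–47% for 20 points at ICC 0.10. That exaggerates the loss, because HR-HPV-negative women are fixed zeros and shrink the between-village variance as well. Variation in positivity between villages would push the ICC back up, so the size of the loss on this denominator stays uncertain.

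The statement on 50 women is fair under the plan's own inputs, where the loss is at most 3.5 points. It needs rechecking only once positives are counted. The 75% at ICC 0.20 is loose wording against the claim for 20 points, and the table discloses it.

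Finally, every loss rests on an assumed positivity. Table 5 gives a specificity of 42.6% for CIN2+, so 57.4% of women without such lesions would test positive. At 57.4% positivity, 10-point power among positives at ICC 0.01 would be about 93%, and 20–50% of all screened would need 35–87% attendance among positives. But Table 5 lists test characteristics, and the Sample size section does not use them as a planning value.

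**Conclusion.** The point holds in a limited form. Table 4 is computed correctly, but for 70 women per village who can all have the event, and nothing in the Sample size section links that to an outcome confined to HR-HPV-positive women.

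If the 70 are screened women and the 20% is attendance among positives, the claim for 10 points at low heterogeneity does not stand over nearly all of the assumed 15–35% positivity range: 51–81% among positives and about 29–74% among all screened, against 98% stated. Among positives it reaches 80% only at about 35% positivity. On that denominator the conclusion for 20–30 points largely survives up to ICC 0.10, and at ICC 0.20 the 20-point figure is 64–72%. On the all-screened denominator power is also below that stated, by an amount that depends on how the ICC rescales and how far positivity varies between villages.

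These figures assume two-sided 0.05 and a normal approximation; a t test on 28 degrees of freedom gives up to about 3 points less at m = 70.

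**What to change.** In the Sample size section:
- State whether the 70 and the 20% refer to screened or to HR-HPV-positive women.
- State an assumed HR-HPV positivity range.
- Recompute Table 4 for the denominator that will be analysed, with the ICC on that same scale, for 50 as well as 70 screened women per village.
- Withdraw or qualify the claim for a 10-point change, and limit the 20-point claim to ICCs up to about 0.10.
- Recheck the statement that 50 women per village makes little difference.

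The cost is one table and a few sentences, and a less favourable stated power. The number of villages and women does not change.

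### The summary sentence claims adequate power for a 20-point change at any ICC, but Table 4 gives 75% at ICC 0.20, a value inside the plan's own plausible range

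*Protocol article*

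**What the plan says.** The Sample size section of the protocol article explains that the number of villages was fixed at the 31 available, and that power was worked out for a range of scenarios:

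- Size: "Power calculations assumed 15 clusters per study arm with an average size of 70 women per cluster".
- Effect: "absolute changes in follow-up rate from the baseline of 20% in one study arm".
- Heterogeneity: power was estimated "across a range of plausible interclass correlation coefficients (ICCs"), and the rows of Table 4 show that range as 0.01, 0.05, 0.10 and 0.20.
- Smaller villages: "Power estimates were repeated using a cluster size of 50 women per village with negligible effect".

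The section then concludes that "we are adequately powered for a 20–30% absolute change in the outcome rate between the study arms", and adds "up to 10% absolute change if low heterogeneity in clusters is found", with a pointer to Table 4. For a 20-point rise, Table 4 gives over 99%, over 99%, 95% and 75% down the four ICC rows. For a 30-point rise it gives over 99% in the first three rows and 98% in the last.

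**The concern.** The conclusion treats the two claims differently. The 10-point claim carries a condition on heterogeneity and the 20–30-point claim carries none, so a reader takes the latter to hold over the whole ICC range just described. Table 4 does not bear that out for 20 points in its bottom row.

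The stake is interpretation. The number of villages cannot be increased. If village-to-village variation turns out to be large, a null result set against this sentence could be taken as adequately powered evidence against a 20-point difference, when by the plan's own figure the power was 75%.

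**Working it through.** **Inputs.** From the Sample size section: 15 villages per arm, 70 women per village, 20% follow-up in one arm, and ICCs of 0.01, 0.05, 0.10 and 0.20. The section states no significance level, so two-sided 5% is my assumption.

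**Formulas.** Effective number per arm: n = 15 × 70 / (1 + 69 × ICC). With difference d and p₂ = 0.20 + d:

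- SE₁ = √{[0.20 × 0.80 + p₂(1 − p₂)] / n}
- Unpooled power = Φ(d / SE₁ − 1.96)
- Pooled power = Φ[(d − 1.96 × SE₀) / SE₁], where SE₀ = √[2p̄(1 − p̄) / n] and p̄ is the mean of the two rates

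**The cell in question (20 points, ICC 0.20).**

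- n = 1050 / 14.8 = 70.9
- SE₁ = √(0.40 / 70.9) = 0.0751
- Unpooled: 0.20 / 0.0751 − 1.96 = 0.70, power 75.9%
- SE₀ = √(0.42 / 70.9) = 0.0769
- Pooled: (0.20 − 1.96 × 0.0769) / 0.0751 = 0.66, power 74.4%

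The printed 75% lies between the two.

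**The other cells.**

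| Rise | ICC | Table 4 | Pooled | Unpooled | t reference, 28 df |
|---|---|---|---|---|---|
| 20 points | 0.05 | > 99% | 99.8% | 99.8% | 99.7% |
| 20 points | 0.10 | 95% | 94.9% | 95.4% | 94.0% |
| 20 points | 0.20 | 75% | 74.4% | 75.9% | 73.0% |
| 30 points | 0.20 | 98% | 97.0% | 97.7% | 96.8% |
| 10 points | 0.01 | 98% | 98.3% | 98.4% | 97.7% |
| 10 points | 0.05 | 71% | 71.0% | 71.4% | 68.4% |

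All 12 cells of Table 4 reproduce within about 1 percentage point by the normal approximation. Of the eight cells for 20 or 30 points, only the 20-point cell at ICC 0.20 is below 80%.

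**Does another reasonable calculation rescue the claim at ICC 0.20?**

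- Beta-binomial simulation with a village-level t-test (20,000 runs): 72.4%.
- 50 women per village: 73.5% pooled, 75.0% unpooled, 72.0% with the t reference.
- One-sided 5%: 83.6%. But a one-sided test does not reproduce the table; for example, it gives 80.8% where Table 4 prints 71%.

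**Where 20 points reaches 80%.** Unpooled: d / SE₁ must equal 1.96 + 0.842 = 2.802, so n = 0.40 × (2.802 / 0.20)² = 78.5. The design effect is then 1050 / 78.5 = 13.38, and ICC = 12.38 / 69 = 0.179. The pooled formula gives 0.173 and the t reference 0.166. At ICC 0.18 all three fall below 80% (79.9%, 78.5% and 77.0%).

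**The case against.** The best defence is that nothing is hidden or miscalculated. The sentence points to Table 4, which is printed with it. The article sets no power target for the primary outcome, so 80% is a convention brought in from outside. Only one cell of eight falls short, at the extreme of the tabulated range. At ICC 0.20 the rise detectable with 80% power is 21.1 points (unpooled), 21.5 (pooled) or 21.9 (t reference), against the 20 claimed. The Statistical analysis section plans to calculate ICCs before the primary analysis, so a careful reader could find the right row. With the villages fixed, no design decision turns on the wording.

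All of that stands, and it makes the point minor. It does not make the sentence agree with the table. The assumptions that the sentence invokes include the full ICC range. The claim survives only if 75% counts as adequate, which the article never says; the one single design power it quotes, for the knowledge survey, is higher ("25 participants per cluster would result in 83% power to detect this target difference").

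The documents do not support three stronger readings that a reader might infer:

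- **That Table 4 overstates power.** Its figures reproduce; only the sentence goes too far.
- **That the 10-point claim also contradicts the table.** It is already limited to low heterogeneity, so 71% at ICC 0.05 is consistent with it.
- **That the sentence is the only account of what the trial can detect.** Table 4 gives three effect sizes at four ICCs.

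**Conclusion.** The summary sentence is wrong as written for a 20-point change and right for a 30-point change. On the plan's own inputs, power for 20 points is at least 95% at ICCs up to 0.10 and 75% at 0.20, which is 5 percentage points below 80%. The recalculated range by formula is 73.0% to 75.9%.

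This rests on two assumptions that the article does not supply: 80% as the meaning of adequate, and a two-sided 5% test. The conclusion would be the same against a 90% standard. The Table 4 inputs are taken as given.

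It would be too much to conclude that the trial is underpowered for 20 points. Three of the four tabulated ICCs give 95% or more, and nothing in the article says that 0.20 is the likely value. Severity is minor.

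**What to change.** Replace the sentence with one that follows the tabulated rows, for example:

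> Power is at least 98% for a 30-point change at all ICCs considered; at least 95% for a 20-point change at ICCs up to 0.10, falling to 75% at 0.20; and 98% for a 10-point change at ICC 0.01, falling to 71% at 0.05.

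If a single limit for the 20-point change is preferred, use an ICC of about 0.17 and say that it is interpolated by formula (0.166 to 0.179 depending on method). A limit of 0.18 would be slightly too generous. Stating the significance level and the power regarded as adequate would settle the remaining ambiguity.

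The cost is one sentence and a slightly less favourable power claim. Table 4, enrolment and design stay as they are.
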